### Interim analyses {21b}

The data safety monitoring board (DSMB) will monitor the study for efficacy and adverse events. Two interim analyses are planned after the inclusion of 50 and 100 patients respectively. For safety reasons, the study will be terminated prematurely if there is a significant increase in critical illness polyneuropathy and myopathy in these interim analyses (i.e. a threefold increase in prevalence) or for futility if there is no difference in the primary outcome measure.

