### Sample size {14}

The primary outcome is the cumulative respiratory morbidity score 12 months after PICU discharge. A classical sample size based on a independent sample *t* test between two groups was calculated, assuming a 20% difference in cumulative mean respiratory morbidity score. This resulted in a required sample size of 148 patients (*N* = 74 intervention versus *N* = 74 placebo) to demonstrate a 20% reduction in respiratory symptoms in the intervention group compared to the placebo with an alpha of 5% and power of 80%. Considering a potential maximum drop-out of 20% per group because of withdrawal of consent or loss to follow-up, we need to enrol *N* = 89 patients per group. Thus, the total sample size is 178 patients.

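### The futility rule is mandatory, has no threshold and is timed by inclusions rather than by 12-month scores; either plausible reading lowers the stated 80% power, one slightly to moderately, the other severely

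*Protocol article*

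**What the plan says.** Under Interim analyses {21b}: "Two interim analyses are planned after the inclusion of 50 and 100 patients respectively". The section then gives two grounds on which the study is to be ended early. One is a rise in critical illness polyneuropathy and myopathy. The other is futility: "or for futility if there is no difference in the primary outcome measure". The wording makes termination the consequence of meeting the criterion, not an option for the board. No p-value, effect size or conditional-power limit is given, and nothing says that the looks wait for follow-up. The same section opens: "The data safety monitoring board (DSMB) will monitor the study for efficacy and adverse events".

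Under Outcomes {12}, the primary outcome is the respiratory morbidity score 12 months after PICU discharge.

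Under Sample size {14}, the calculation is for a fixed two-group comparison of means, "assuming a 20% difference in cumulative mean respiratory morbidity score", "with an alpha of 5% and power of 80" per cent. "This resulted in a required sample size of 148 patients", raised to 178 for a "potential maximum drop-out of 20% per group". The interim looks are not mentioned.

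The section on the data monitoring committee {21a} repeats the 50 and 100 timing and refers to a separate DSMB document, which is not shown.

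**The concern.** This is a rule that the article states, with a trigger and a criterion, and both are badly fixed.

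The trigger counts inclusions, while the outcome arrives at least a year later. A look at 50 inclusions would therefore rest on few scores.

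The criterion can be read in at least two ways. With 25 or fewer children per arm, a non-significant difference is the expected result even when the drug works as the design assumes. If the board reads no difference that way, the rule is likely to end a trial of an effective drug, and the resulting null could not be interpreted. If it reads the words as no observed benefit, the damage is much smaller. That choice would have to be made with the interim data on the table.

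**Working it through.** **Inputs.** From Sample size {14}: 74 evaluable per arm, alpha 5% (taken as two-sided), power 80%, drop-out 20%, 178 enrolled. From Interim analyses {21b}: looks at 50 and 100 inclusions. From Trial status: enrolment from 1 May 2019 to August 2024, about 63 months.

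**Design effect.** No mean or SD is given, so 148 cannot be derived independently. Solved backwards by the normal approximation:

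d = (1.960 + 0.842) × √(2/74) = 0.461 (0.464 with the t distribution).

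A 20% difference then means an SD of 0.20/0.461 = 43% of the control mean. A one-sided alpha would give d = 0.409.

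**Scores available at each look (PICU stay ignored).**
- Uniform accrual: 178/63 = 2.83 per month, so 2.83 × 12 = 33.9 children are still inside the 12 months. At 50 inclusions 50 − 33.9 = 16 have reached 12 months; at 100 inclusions, 66. That is 8 and 33 per arm, or 6 and 26 after 20% drop-out.
- Slow start (assumed 10 to 40 children by August 2021, the rest over 36 months): 9 to 26 of 50, and 44 to 54 of 100.
- Constant 178/36 = 4.9 per month: 0 of 50, and 41 of 100.

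**A single look with n per arm, design effect true.**
- P(not significant) = Φ(1.96 − d√(n/2)). For n = 25: d√12.5 = 1.628, giving Φ(0.332) = 63%. For n = 50: 37%.
- P(estimate ≤ 0) = Φ(−d√(n/2)). For n = 25: 5%. For n = 6: 21%.

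**Both looks together.** Simulation of 400,000 trials at d = 0.461, final analysis at 74 per arm. The trial stops if either look meets the rule. Power without looks is 80%.

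| Scores per arm at looks 1 / 2 | Not significant: stopped / power | Estimate not favouring rocuronium: stopped / power |
|---|---|---|
| 25 / 50 (all scores exist) | 66% / 33% | 6% / 78% |
| 20 / 40 (20% drop-out, no lag) | 73% / 26% | 8% / 77% |
| 8 / 33 (uniform accrual, lag) | 88% / 11% | 19% / 68% |
| 6 / 26 (lag and drop-out) | 91% / 8% | 23% / 65% |
| 0 / 20 (4.9 per month; look 1 has no data) | 69% / 29% | 7% / 77% |

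With d = 0.464, the best case in the right-hand column becomes 5% stopped and 79% power. If the final analysis has 89 × 0.8 = 71 per arm, the worst case becomes 64% power.

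**An explicit rule, for comparison.** With t = n/74, θ = d√(74/2) = 2.80 and interim statistic Z, conditional power under the design effect is 1 − Φ[(1.96 − Z√t − θ(1 − t))/√(1 − t)]. Stopping when this is below 20% ends at most 5.5% of effective trials in these cases. Power stays within about half a percentage point of 80%. A 10% limit costs less still.

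**The case against.** The strongest reply is that the text never says *not significant*. The same sentence uses the word significant for the neuromuscular safety criterion and leaves it out of the futility clause. A reader might infer from the rule that an effective drug would probably be abandoned. The document does not support that as a flat statement, because it holds only under the non-significance reading. Under the other reading with complete scores, the loss is one or two percentage points of power. This objection stands and limits the conclusion. It does not rescue the rule, because one sentence then allows power anywhere from about 79% down to about 8%.

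A reader might also infer that most scores are missing at both looks. That is well supported at 50 inclusions, where only the most favourable accrual pattern tried reaches 26 of 50 before drop-out. It is not clear at 100, where about 41 to 66 of 100 could exist. Uniform accrual is itself an assumption: Trial status reports that one centre had started and that inclusion was slower than expected.

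A reader might further infer, from the statement that the board monitors efficacy, that the two looks inflate the type I error. The document does not support this. It names two stopping grounds, neuromuscular harm and futility, and no early efficacy claim. Stopping only for futility does not raise the type I error.

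Finally, the DSMB document may define the rule more closely. It may add detail, but it should not have to overrule a published instruction to terminate.

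**Conclusion.** The concern holds in a limited form. The futility rule is mandatory as written, has no threshold, and is triggered by inclusions for an outcome that is known a year later. The 80% power is a fixed-design figure that does not allow for it. Every case examined lowers that power: by 1 to 16 points if no difference means an estimate not favouring rocuronium, and to about 8–33% if it means not significant. The severe result does not need the follow-up lag, since 66% of effective trials stop even with all scores in hand.

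The figures assume a two-sided 5% test, an approximately normal outcome, an effect solved back from 74 per arm, and the accrual patterns shown. No claim is made about type I error.

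**What to change.** Amend Interim analyses {21b} and the matching DSMB text as follows.

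1. Trigger any look at the primary outcome by the number of completed 12-month scores. Keep the 50-inclusion look for safety only.
2. Replace the no-difference wording with a non-binding futility boundary, for example conditional power under the design effect below a fixed value in the range 10–20%.
3. State that there is no early stopping for efficacy, so that no alpha adjustment is needed.
4. Report in Sample size {14} the power that results with the boundary in place.

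The cost is a short amendment and an edit to the DSMB document, with no added patients. The downside is a later and less frequent chance to stop. Under uniform accrual and 20% drop-out, 50 completed scores need 50/0.8 = 62.5 children past 12 months, reached at about 62.5 + 33.9 = 96 inclusions. For 100 scores the figure is 125 + 33.9 = 159 of 178 inclusions, so a second futility look that late would spare few children.

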### Methods for additional analyses (e.g.) subgroup analyses) {20b}

There will be no subgroup analyses performed.

### Methods in analysis to handle protocol non-adherence and any statistical methods to handle missing data {20c}

All study participants who have received a dose of the study drug will be included in a modified intention to treat analysis. Participants who have received the study drug during 48 h and with a respiratory morbidity score 12 months after discharge (primary outcome measure) will be included in the per-protocol population.

### Plans to give access to the full protocol, participant level-data and statistical code {31c}

The datasets analysed during the current study are available from the corresponding author upon reasonable request after obtaining approval of the use by all members of the investigative team.

## Oversight and monitoring

## Composition of the coordinating centre and trial steering committee {5d}

The trial steering committee is composed of the principal investigator (PI) and eight co-investigators, who all contributed to and approved the final protocol. The PI is responsible for oversight of the entire study. The co-investigators collaborated to the drafting of the study protocol, including the pulmonary function testing done at follow-up and the neurological muscle strength assessment during PICU admission. One co-investigator oversees the production and handling of the study medication, another one contributes to the implementation strategy and one co-investigator is responsible for the health care technology assessment. There is one research nurse on the steering committee and one biostatistician. Each participating site has a local PI who is responsible for the conduct of the study at their site and a research nurse to assist.

### Composition of the data monitoring committee, its role and reporting structure {21a}

There is a Data Safety and Monitoring Board (DSMB) for this study, composed of one paediatric intensivist who chairs the DSMB, two adult-based intensivists and one biostatistician/epidemiologist. Roles and responsibilities of the DSMB are detailed in a DSMB document. The DSMB meets at least once a year; the exact frequency of meetings will depend on trial events. Two interim analyses by the DSMB are planned after 50 and 100 inclusions.

### Adverse event reporting and harms {22}

For this study, the following adverse events (AE) are defined pneumothorax, decubitus, CIPNM, VAP, withdrawal syndrome, delirium, hypotension or tachycardia in response to study medication with need for intervention by means of medication or fluid challenge, allergic reaction and reintubation. These AEs will be recorded in the database. A serious adverse event (SAE) is any untoward medical occurrence or effect that cannot be attributed to the underlying disease or that can be expected in the natural disease course of paediatric acute respiratory distress syndrome. For this study, the following SAEs are defined death (all-cause mortality), hypersensitivity or an allergic reaction that is not attributable to any concurrent medication, defined by skin rash and/or hypotension and/or severe bronchospasm necessitating the use anti-histaminic drugs and corticosteroids and/or vasopressors, cardiac arrhythmias or dysrhythmias and clinically relevant incidents, judged by the investigator, which are unexpected within the natural course of PARDS. An elective hospital admission will not be considered as a serious adverse event.

The risks associated with this study are minimal based on the following arguments
Patients in the intensive care unit are under constant tight observation, so any change in vital parameters is noted immediately. Furthermore, patients with severe lung injury are commonly deeply sedatedBlood samples are only taken from an indwelling arterial catheter or central venous catheter, which are already in place for clinical purposes. Blood samples for this study will be combined as much as possible with routine blood sampling part of daily clinical careEndotracheal suctioning is routinely performed in mechanically ventilated patients by nurses taking care of the patients; for this study suctioning specimens are collected to measure the pulmonary inflammatory responseThe investigational drug is commonly used in (paediatric) critical care; hence, there is a good understanding of this drug.

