#### Secondary outcome measures

Secondary outcomes include LCI and FRC measured using multiple breath wash-out 12 months after PICU discharge, and the level and time course of the cumulative respiratory morbidity score assessed at baseline, 3, 6 and 9 months after PICU discharge. Secondary outcome measures related to the acute phase of disease (i.e., during PICU admission) include level and time course of ventilator settings (peak inspiratory pressure, plateau pressure, mean airway pressure, driving pressure, PEEP, set rate, total rate, inspiratory time), respiratory system mechanics (quasistatic compliance, dynamic compliance, respiratory system resistance), metrics of oxygenation (SpO_2_/FiO_2_ ratio, PaO_2_/FiO_2_ ratio, OI, OSI) and ventilation (PCO_2_, pH), and hemodynamic parameters (heart rate, blood pressure, central venous pressure, daily cumulative fluid balance, number of fluid challenges). We will measure the level and time course of the non-respiratory pediatric logistic organ dysfunction 2 (PELOD – 2) score as measure of organ dysfunction and pediatric Risk, Injury, Failure, End-stage renal failure (pRIFLE) criteria for acute kidney injury, the number of adverse drug reactions, and re-intubations [27, 28]. We will study the level and time course of the pulmonary and systemic inflammatory response, the prevalence of critical illness polyneuropathy and myopathy, and ventilator-associated pneumonia.

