## Assignment of interventions: Blinding

### Who will be blinded {17a}

Full blinding of the clinical team cannot be ensured because children randomised to the control arm may display spontaneous movements and/or breathing. For this reason, the study team will be prohibited from participating by any means in the clinical care of the participant. On top of that, the statistical analysis and long-term outcome assessment staff are blinded to the study arm, and aggregate outcome data will be restricted to an unblinded statistician and the data safety monitoring board.

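### Treated hypotension or tachycardia and adverse drug reactions are counted only after a causal judgement with no stated blinded assessor, and the SAE definition contradicts its own list

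*Protocol article*

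**What the plan says.** All references are to the protocol article.

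- **Adverse event reporting and harms {22}, AE list.** One item is "hypotension or tachycardia in response to study medication with need for intervention by means of medication or fluid challenge". In the same list, pneumothorax, decubitus, critical illness polyneuropathy and myopathy (CIPNM), ventilator-associated pneumonia, withdrawal syndrome, delirium, allergic reaction and reintubation carry no study-drug condition.
- **Secondary outcome measures.** These include "the number of adverse drug reactions, and re-intubations". They also include the course over time of heart rate, blood pressure and the number of fluid challenges, whatever the cause.
- **Who will be blinded {17a}.** The section opens by conceding a limit: "Full blinding of the clinical team cannot be ensured because children randomised to the control arm may display spontaneous movements and/or breathing". In response, "the study team will be prohibited from participating by any means in the clinical care of the participant". The staff named as blinded are those doing the statistical analysis and the long-term outcome assessment.
- **Adverse event reporting and harms {22}, SAE definition.** The general sentence covers an occurrence that "cannot be attributed to the underlying disease or that can be expected in the natural disease course of paediatric acute respiratory distress syndrome". The list that follows names all-cause death, certain allergic reactions, arrhythmias or dysrhythmias, and "clinically relevant incidents, judged by the investigator, which are unexpected within the natural course of PARDS".

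**The concern.** An event that counts only if it is blamed on the study drug measures two things at once: how often the event happens, and how readily someone makes that attribution. In a fully blinded trial the second part is similar in both arms and largely cancels. Here the arm may be guessed, because a child who moves or breathes spontaneously is unlikely to be on rocuronium. If the guess influences the causal judgement, the recorded counts can differ between arms when the true rates are equal, or agree when they are not.

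This matters because the article's Discussion wants the use of neuromuscular blockade weighed against side effects. It also cannot be repaired at analysis: an episode never entered as an adverse event, because nobody blamed the infusion, is missing from the adverse event data.

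The SAE wording is a separate problem of consistency. If two sites can read the definition in opposite senses, SAE counts may not mean the same thing across sites.

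**Working it through.** **Step 1. Which safety items need a causal judgement?**

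| Item | Needs a causal judgement? |
|---|---|
| Treated hypotension or tachycardia (AE) | Yes, to study drug |
| Number of adverse drug reactions (secondary outcome) | Yes, by its nature |
| Clinically relevant incidents (SAE) | Yes, investigator judges whether unexpected in PARDS |
| Allergic reaction as an SAE | In part: must not be attributable to concurrent medication |
| All other listed AEs | No study-drug condition |
| All-cause death; arrhythmias (SAE) | No |
| CIPNM stopping rule (Interim analyses {21b}) | Not to study drug |
| Heart rate, blood pressure, fluid challenges | No |

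**Step 2. Who judges, and could they know the arm?** The harms section names a judge (the investigator) only for the last SAE item. For the haemodynamic AE and the adverse drug reactions no assessor is named. Research nurses and/or site investigators collect the data (Exploratory outcome measures, under Plans for assessment and collection of outcomes {18a}), and the study team stays out of clinical care. The clinical team may infer the arm, as section {17a} says. Data collectors are not clearly protected either: set rate and total rate are both read from the ventilator, and a total rate above the set rate indicates spontaneous breathing.

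**Step 3. How much could it matter?** The article gives no event rate and no attribution share, so there is no planned figure to reproduce. The following is illustration only. Inputs: n = 89 per arm (Sample size {14}); true rate p, equal in both arms (assumed); shares attributed to study drug a₁ and a₂ (assumed). Recorded rates are p₁ = p·a₁ and p₂ = p·a₂, so the apparent risk ratio is a₁/a₂. With p̄ = (p₁ + p₂)/2, the chance of a false significant difference at two-sided 5% is approximately

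Φ{ [|p₁ − p₂| − 1.96·√(2p̄(1 − p̄)/n)] / √([p₁(1 − p₁) + p₂(1 − p₂)]/n) }.

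Worked case: p = 0.30, a₁ = 0.60, a₂ = 0.40. Then p₁ = 0.18, p₂ = 0.12 and p̄ = 0.15. The first root is 0.0535 and the second 0.0533. (0.06 − 1.96 × 0.0535)/0.0533 = −0.84, and Φ(−0.84) = 0.20. Expected recorded events are 89 × 0.18 = 16.0 and 89 × 0.12 = 10.7.

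| Attributed, one arm v other | Apparent ratio | p = 10% | p = 20% | p = 30% | p = 50% |
|---|---|---|---|---|---|
| Equal shares | 1.0 | 5% | 5% | 5% | 5% |
| 60% v 40% | 1.5 | 9% | 14% | 20% | 34% |
| 80% v 40% | 2.0 | 20% | 37% | 55% | 84% |

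Swapping the arms leaves these chances unchanged and inverts the ratio (40% v 60% gives 0.67). The table therefore says nothing about direction.

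**Step 4. The SAE wording.** The general sentence joins two conditions by *or*: not attributable to the underlying disease, or expected in the natural course of PARDS. The last list item requires the opposite of the second condition. Read literally, the general sentence makes expected PARDS events SAEs; the list item excludes them. Both cannot be applied to the same event.

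**The case against.** The strongest reply is that little of the safety evidence is exposed. Most listed AEs, all-cause death, arrhythmias and the CIPNM stopping rule need no attribution to study drug, and heart rate, blood pressure and fluid challenges are compared whatever the cause. This stands, and it confines the point to the items named. It does not remove the point, because episodes treated with medication are not among the cause-free haemodynamic outcomes listed.

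A reader might infer that bedside staff who see the paralysis make the attribution. The article does not say so. It names no assessor for these items, separates the study team from care, and says only that control children may move; it also notes that patients with severe lung injury are commonly deeply sedated. What can be said is that no blinded assessor is stated.

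A reader might also infer that any bias must run against rocuronium. The article does not support a direction. Under Relevant concomitant care {11d}, a persistent rise in heart rate and blood pressure is read as insufficient comfort, and the behavioural comfort score cannot be used in paralysed patients. Tachycardia in a motionless child might therefore be put down to discomfort rather than to the infusion.

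On the SAE sentence, the fair defence is that a negation was probably lost, that the list is the operative part, and that the full protocol and the DSMB document are not shown. That may be so. It makes the correction easy, but the printed text still conflicts. It would go too far to say that sites will in fact report different counts, or that a pneumothorax could go unrecorded: pneumothorax is an unconditional AE, and only its SAE label would be in doubt.

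**Conclusion.** The point holds in limited form. Treated hypotension or tachycardia, the adverse drug reaction count and the investigator-judged SAEs are at risk of differential ascertainment between arms, because each rests on a causal or expectedness judgement with no stated blinded assessor in a trial whose clinical team may infer the arm. Calling the safety comparison as a whole biased is not supported. Size and direction are unknown: the illustrated 9% to 84% chances of a false significant difference, against 5% with equal attribution, rest entirely on assumed event rates and attribution shares. Separately, the general SAE sentence and the SAE list contradict each other on whether expected events qualify, and this needs no assumption. Neither point affects the primary outcome, the sample size or the power.

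**What to change.** 1. In the AE list, delete the condition that the event be a response to study medication. Record every episode of hypotension or tachycardia treated with medication or a fluid challenge, in both arms, over one fixed window starting at the study bolus. Compare all-cause counts, alongside the heart rate, blood pressure and fluid-challenge data already collected.
2. Keep the causality judgement, including the adverse drug reaction count, as a descriptive secondary column. The adverse drug reaction outcome should not be turned into an all-cause count, since that would be a different outcome.
3. Reconcile the general SAE sentence with the SAE list so that all sites apply one definition. Redefining every SAE by its outcome alone is not required for this and is a debatable trade-off in an intensive care population.

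The cost is protocol and case report form wording, plus more disease-related events recorded in both arms. One weakness remains: whether an episode is treated is still decided by a possibly unblinded team, so the all-cause count is less open to bias rather than free of it. The cause-free heart rate and blood pressure data are a useful cross-check.

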### Criteria for discontinuing or modifying allocated interventions {11b}

An investigator may discontinue or withdraw a patient from the study for the following reasons:
withdrawal of informed consent by the parents or the legal caretakerssigns of hypersensitivity or an allergic reaction that is not attributable to any concurrent medication, defined by skin rash and/or hypotension and/or severe bronchospasm necessitating the use of anti-histaminic drugs and corticosteroids and/or vasopressorscannulation for extra-corporeal life support (ECLS)

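### The general SAE sentence in section {22} contradicts its own paragraph on expected events, and the hypersensitivity wording in {22} and {11b} leaves hypotension treated with a vasopressor alone open to two classifications

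*Protocol article*

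**What the plan says.** Three pieces of text in the protocol article matter here.

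**General SAE sentence, section {22}.** An SAE is any untoward occurrence or effect that "cannot be attributed to the underlying disease or that can be expected in the natural disease course" of PARDS. A study-specific list follows: all-cause death, hypersensitivity or allergic reaction, cardiac arrhythmias, and a closing entry for incidents that the investigator judges clinically relevant and that are not expected in the natural course of PARDS.

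**AE and SAE entries for drug reactions, section {22}.** The AE list includes "hypotension or tachycardia in response to study medication with need for intervention by means of medication or fluid challenge, allergic reaction and reintubation". Of the listed AEs the article says "These AEs will be recorded in the database". The SAE list has "hypersensitivity or an allergic reaction that is not attributable to any concurrent medication", which is "defined by skin rash and/or hypotension and/or severe bronchospasm necessitating the use anti-histaminic drugs and corticosteroids and/or vasopressors".

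**Discontinuation, section {11b}.** "An investigator may discontinue or withdraw a patient from the study for the following reasons": one of the three reasons is signs of such a reaction, with the same definition apart from one small word.

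**The concern.** The general SAE sentence tells sites what to report as serious. Its second limb brings in events that are expected in PARDS, whereas the closing list entry brings in only events that are not. A site following the first would report ordinary PARDS events as SAEs. A site following the second would not.

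The hypersensitivity definition governs both SAE reporting and an optional reason to stop. A fall in blood pressure after the bolus that is treated with a vasopressor sits at its boundary, and the text does not settle on which side it falls.

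Safety reporting is what is at stake. The SAE counts that reach the DSMB would partly reflect how each site read the sentence. Section {17a} concedes that the clinical team cannot be fully blinded, so loosely defined classification could differ by arm as well as by site. Study drug stopped before 48 h also takes a child out of the per-protocol population in section {20c}.

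**Working it through.** No arithmetic applies. The check sets the texts side by side.

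**1. Expectedness.** The general sentence, taken literally, makes an event an SAE if it is not attributable to the disease *or* is expected in PARDS. The closing list entry, for a clinically relevant incident, requires that it is not expected. The four possible combinations give:

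| Attributable to underlying disease | Expected in PARDS | General sentence as printed | Closing list entry |
|---|---|---|---|
| Yes | Yes | SAE | Not SAE |
| Yes | No | Not SAE | SAE |
| No | Yes | SAE | Not SAE |
| No | No | SAE | SAE |

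The two texts agree in one row of four. The first row matters most, because it holds the ordinary course of the disease.

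A negation has probably been lost. Restoring it while keeping *or* (not attributable, or not expected) mends the first two rows but still makes the third an SAE. Changing *or* to *nor* (neither attributable nor expected) mends the first and third rows but leaves the second in conflict. The sentence therefore has to be rewritten around a stated expectedness condition. Death, hypersensitivity and arrhythmia carry no expectedness condition of their own, so the conflict lies between the general sentence and the closing entry.

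**2. Allergic reaction.** The AE entry has no qualifier. The SAE entry adds that the reaction is not due to a concurrent drug, shows named signs and needs named treatment. A milder reaction, or one due to another drug, is an AE only. One that meets the qualifiers is both. This is ordinary nesting, though the article does not say so.

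**3. Hypotension after study drug.** The treatment phrase can be grouped as:

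- A: (antihistamines and corticosteroids) and/or vasopressors
- B: antihistamines and (corticosteroids and/or vasopressors)

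| Treatment given | AE entry | Sign and treatment part of SAE entry, A | Same, B |
|---|---|---|---|
| Fluid challenge only | Met | Not met | Not met |
| Vasopressor alone | Met | Met | Not met |
| Antihistamine and corticosteroid | Met | Met | Met |
| Antihistamine and vasopressor | Met | Met | Met |

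Among these, only the vasopressor-alone case changes with the grouping. Under A it can be an SAE and a possible reason to discontinue if the event is also judged to be hypersensitivity. Under B it cannot.

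**4. Attribution.** The definition excludes concurrent medication and is silent on underlying illness. Section {22} names the reaction itself and {11b} names signs of it, so the two places do not tie the clinical judgement to the event in quite the same way.

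**The case against.** The strongest reply is that overlap is not contradiction. An SAE is normally also an AE, recording an event does not bar reporting it as serious, and {11b} is permissive and uses the same definition as {22}. This stands. A reader might infer that sites are given opposite rules for the same reaction, but nothing in {22} requires treatment to continue after a listed AE, and nothing in {11b} requires it to stop.

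A reader might also infer that septic hypotension on a vasopressor meets the SAE and discontinuation wording, and multiply some rate of vasopressor use by the 178 children. The documents do not support this. The event must first be hypersensitivity or an allergic reaction, and the sign-and-treatment test is met by a vasopressor alone only under grouping A. The documents also give no rate of vasopressor use.

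It can further be said that sites will work from the specific list and ignore the general sentence. That limits the practical effect but does not remove it, because the closing list entry is open-ended and rests on the investigator's view of what is expected, where the general sentence points the other way.

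The consequences are also bounded. The number of adverse drug reactions counts a reaction under either label. The stated stopping triggers are critical illness polyneuropathy and myopathy and futility, and a dosed child stays in the modified intention-to-treat analysis.

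Finally, the full protocol may give a reporting hierarchy, so its absence from the article is no finding. The printed SAE sentence and the ambiguous treatment phrase are different in kind: they are stated rules, not omitted detail.

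**Conclusion.** Two wording defects hold. The first is firm: the general SAE sentence is wrong as written, and taken literally it conflicts with the closing entry of its own paragraph in three of four combinations of attribution and expectedness. The second is narrower: the treatment phrase in {22} and {11b} has two readings, which differ for hypotension after study drug treated with a vasopressor alone. Sites can class that event differently. They are not under contradictory orders.

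The effect falls on safety reporting, optional discontinuation and, through early stopping, the per-protocol population. It cannot be sized in numbers of children from these documents. The conclusion assumes that sites apply the wording as printed in the article. Correction is worthwhile because the rule is operative, the cost is small, and the trial status section says that only one of the five planned centres had started.

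**What to change.** - Rewrite the general SAE sentence in {22} so that it agrees with the paragraph's closing entry on unexpected events. State how attribution and expectedness combine, since inserting a negation alone does not do it.
- State that the SAE hypersensitivity entry is the qualified subset of the AE entries. Keep allergic reaction on both lists: dropping it from the AE list would lose milder reactions, and dropping it from the SAE list would take serious status from the severe ones.
- Make the sign and treatment wording unambiguous and identical in {11b} and {22}, so that vasopressor-alone hypotension has one classification. Say how hypotension explained by underlying illness is treated.
- Carry the wording into the AE form.

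Which events should end study drug is for the sponsor to decide. The cost is a few sentences and a form change, with no added procedures.
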